# B1. PURPOSE OF PROTOCOL

| To evaluate the effects of Tai Chi—a mind-body exercise––on age-related loss of physiological complexity (using fractal and entropy based measures), and to understand the relationship between complexity, function and adaptability, we will conduct a two-arm prospective randomized clinical trial. Our overarching goal is to evaluate if six months of Tai Chi training, compared to a waitlist control receiving standard medical care, can enhance physiological complexity and adaptability in older Tai Chi-naïve adults. Secondary goals of the study are to characterize the relationship between complexity biomarkers, measures of function, and resilience. This pilot study will inform a future more definitive trial by providing information on recruitment and retention, compliance, dose-dependent effects, preliminary estimates of effect size, and the optimal biomarkers of complexity, function, and adaptive capacity.    **Specific Aim #1: To determine if 6 months of Tai Chi training can increase complexity, function, and adaptive capacity of multiple physiological systems in older healthy adults.** Sixty healthy older adults (50-79y) naïve to Tai Chi will be recruited from the Boston community and randomized to either 6 months of Tai Chi training or to a waitlist control. Measurements of complexity, adaptive capacity, and function will be assessed at baseline, 3, and 6 months. Dynamics of cardiovascular (heart rate), balance (center-of-pressure displacement), and locomotor (gait stride interval) systems will be quantified using indices derived from two complementary analytic methods developed by members of our team––detrended fluctuation analysis^26^ and multi-scale entropy.^6^ Function will be characterized by exercise capacity, clinical measures of balance, lower and upper extremity strength, cognitive function, and health related quality of life. Adaptability of multiple physiological systems will be assessed using common perturbations including: heart rate responses to posture change, center of pressure (i.e. balance) responses to a dual cognitive task and closed eyes, and c) gait responses to dual cognitive task. In addition to informing the feasibility of a future trial, outcomes will provide preliminary data to evaluate the following hypotheses.  ***Hypotheses*** *Compared to the control group:*  *H.1.a) Those who participate in Tai Chi will exhibit higher levels of complexity across all measured physiological systems;*  *H.1.b) Those who participate in Tai Chi will exhibit higher levels of physical and cognitive function;*  *H.1.c) Those who participate in Tai Chi will exhibit higher levels of adaptive capacity;*  *H.1.d) The magnitude of the effects of Tai Chi on physiological complexity, function and adaptive capacity in healthy older adults will be positively correlated with age.*  **Specific Aim #2: To determine the relationships between biomarkers of physiological complexity, conventional measures of function and adaptive capacity.** Statistical regression models will be used to determine relationships, both at baseline and overtime, between a) complexity biomarkers and measures of physical and cognitive function, and b) complexity biomarkers and adaptive capacity. Elucidating these relationships will further inform the interpretation of complexity biomarkers and provide insights into underlying component mechanisms contributing to complex physiological dynamics.  ***Hypotheses*** *At baseline:*  *H.2.a) Measures of complexity are positively correlated with physical and cognitive function;*  *H.2.b) Measures of complexity are positively correlated with adaptive capacity.*  *Over time:*  *H.2.c) Changes in complexity are positively correlated with changes in physical and cognitive function;*  *H.2.d) Changes in complexity are positively correlated with changes in adaptive capacity.*  **Specific Aim #3: To determine cross-sectionally if long-term Tai Chi training (> 5 years) is associated with greater complexity, function, and adaptive capacity of multiple physiological systems in older healthy adults, when compared with Tai Chi naïve and novice (≤ 6 months training) Tai Chi practitioners**  ***Hypotheses*** *Compared to Tai Chi naïve and novice Tai Chi practitioners:*  *H.3.a) Long-term Tai Chi practitioners will exhibit higher levels of complexity across all measured physiological systems;*  *H.3.b) Long-term Tai Chi practitioners will exhibit higher levels of physical and cognitive function;*  *H.3.c) Long-term Tai Chi practitioners will exhibit higher levels of adaptive capacity;*  *H.3.d) The magnitude of the effects of long-term Tai Chi training on physiological complexity, function and adaptive capacity in healthy older adults will be positively correlated with age.*  **Specific Aim #4: To determine cross-sectionally if age is associated with greater complexity, function, and adaptive capacity of balance and gait in young healthy adults, when compared with to older adults**  ***Hypotheses*** *Compared to older adults and a young adult comparison group:*  *H.3.a); The magnitude of physiological complexity, function and adaptive capacity will be positively correlated with age.*  *H.3.b) Young adults will exhibit higher levels of adaptive capacity of balance and gait.* |

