### Statistical Considerations

| ***Sample Size Justification:*** Our analysis will be based on a longitudinal regression analysis in which we do not have an estimate of the within-participant correlations. In the worst case, the two follow-up measures provide no more information than a single follow-up, and the power calculation is equivalent to that for a simple t-test. With 30 participants in each group, we would have 50% power to detect an effect size of 0.52 (i.e., the sample size provides 50% sensitivity to detect a difference between groups .52 times the standard deviation of the outcome measure) and 80% power to detect an effect size of 0.74 for each of the main effects. Our primary hypothesis, however, is an interaction effect. Our sample size provides at least 50% power to detect an interaction effect size of 1.03, under this worst-case scenario. At the other extreme, if the two follow-up observations are independent, we will have 50% power to detect an interaction effect size of 0.72 and 80% power to detect an effect size of 1.03. The use of regression models further increases power by accounting for additional sources of variability. In our heart failure study, the mean difference in MSE change between Tai Chi and control was 2.26, which translates to an effect size of 1.2. Preliminary COP data from our Tai Chi for osteopenia study showed a similar effect. Therefore, we think changes of this magnitude will likely be present in the proposed study and our study has adequate power.  For Study Aim 3, we will in essence be comparing the 30 tai chi experts to the 60 novices. After adjusting for the effect of age, we will have 80% power to detect a difference between naïve and tai chi experts of approximately 0.65 times the residual error.  For Study Aim 4, we will be comparing the baseline COP and balance measures in the various age categories (15 participants age 25-35, and 20 participants in each of the older groups). This sample will provide at least 82% power to detect a difference between the young group and the average of the older groups equal to the within-group standard deviation.  ***b. Data Analysis***  *Aim 1*: We are interested in comparing the change over time in the Tai Chi students versus the controls. The primary analysis will use an intention-to-treat paradigm, i.e., participants will be evaluated on the basis of group assigned by randomization without regard to subsequent adherence. Since this is a pilot study, we will not impute values for missing data; however, the statistical models we are using will include all available data. We recognize that some participants may drop out before the follow-up evaluation and that some outcome measures may not be evaluable for some participants. We will make no adjustment for multiple testing. A secondary ‘per-protocol’ analysis will be limited to participants who were compliant (attended 70% of classes and completed at least 70% of home sessions).  Our primary analysis will employ linear mixed effects regression models that examine change over time (i.e., slope) for each outcome measure (i.e., the complexity measures, MSE and detrended fluctuation analysis) for each of the systems (i.e., heart rate, balance and gait). The models will incorporate a random intercept and a random slope for each participant. The models will be of the form:  ****  for individual  in treatment group  where the random intercept , the random slope , and the residual error . The focus of the primary analyses is on , which evaluates whether treatment is associated with the slope over time.  We will also conduct sensitivity analyses that incorporate additional covariates into the models, including age, gender, baseline physical and mental health, BMI, expectancy, and exercise behavior. We are particularly interested in examining age with a focus on assessing whether age substantially reduces the variability of the random effects, i.e., whether it explains a substantial proportion of between-person variability in baseline complexity and slope.  Analyses of secondary outcomes will follow the same general analytic approach. We will use mixed effects models to examine the effects of Tai Chi training over time on physical and cognitive function (exercise capacity, balance, upper and lower extremity strength, cognitive function, and quality of life) and adaptive capacity (change in heart rate, change in COP displacement, change in stride variability).  *Aim 2*: We hypothesize that function and adaptive capacity are associated with complexity. We will first examine the association between complexity measures and function/adaptive capacity at baseline. We will calculate Pearson correlation coefficients between the complexity measures (MSE and detrended fluctuation analysis) and the measures of function/adaptive capacity. To examine the independent association between complexity and function/adaptive capacity, we will fit ordinary least squares regression models using the function/adaptive capacity measures as the dependent variable. Independent variables will include age and sex as well as any other baseline characteristics associated with the function variable. We will add the complexity measure to this model and evaluate the Wald test and the change in R^2^.  We will also investigate whether changes in complexity are associated with changes in function/adaptive capacity. We will fit linear regression models with change in function/adaptive capacity as the dependent variable and change in complexity as the independent variable of interest. Since we will have 2 observations per participant (change at 3 months and change at 6 months), we will use generalized estimating equations methods (GEE) to account for the within-person correlation. Independent variables will include the measure of function/adaptive capacity at baseline, age, sex, treatment group and time (3 vs. 6 month).  Further, we hypothesize that complexity is the primary mediator of the association between Tai Chi and improvements in adaptive capacity. We will examine this using the approach recommended by Judd and Kenny.^193^ For example, to examine whether multi-scale entropy of balance mediates the effect of Tai Chi on center of pressure response to a dual cognitive task among the older participants, we will fit 3 regression models: regress MSE on Tai Chi use; regress COP response on Tai Chi; and regress COP response on MSE and Tai Chi use. The associations seen in these models determine the existence and strength of mediation.  Despite the implicit directionality of our hypotheses, all tests will be two-sided. We recognize that we are examining a moderate number of outcomes in this study. Since it is a pilot study and has limited power, we do not intend to adjust for multiple testing.  *Aim 3:* Our goal is to compare the complexity measures, function, and resilience to perturbations between tai chi experts and those with no tai chi training or only limited training. We expect responsiveness to decrease as a function of age among the tai chi naïve participants (i.e., both randomized groups combined). We hypothesize that tai chi experts will have a generally higher level of responsiveness, and that their responsiveness will decline with age at a slower rate than naïve or novice practitioners. To examine these questions, we will fit linear regression models to the baseline responsiveness measures for all participants:    where TC is an indicator variable for the tai chi experts.  is an estimate of the difference in responsiveness between tai chi experts at age 50,  is an estimate of the change in responsiveness per year for the novice group, and is the difference in rate of change between novices and tai chi experts.  We will fit a similar model to compare the tai chi experts to the naïve and novice groups using the 6-month data for the randomized patients and the baseline data for the tai chi experts. The group variable will be a categorical variable with 3 levels.  *Aim 4:* We will calculate sample means for each of the outcomes in each age group. We will use standard one-way analysis of variance to compare the four groups. If the overall test is significant, we will use Dunnett’s test to compare the young group to each of the older age groups. |

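### The age analysis stated for Aim 1 is not specific to H.1.d: it looks at variance explained by age, and no treatment x age x time term is stated

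*Protocol*

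**What the plan says.** Section B1 lists four hypotheses under Aim 1. The fourth, H.1.d, reads: "The magnitude of the effects of Tai Chi on physiological complexity, function and adaptive capacity in healthy older adults will be positively correlated with age". It covers complexity (the primary outcomes) as well as function and adaptive capacity (the secondary outcomes).

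Under Statistical Considerations, the Aim 1 primary model is a linear mixed model with random intercept and slope. Its focal coefficient is the one "which evaluates whether treatment is associated with the slope over time". Age comes in afterwards: "We will also conduct sensitivity analyses that incorporate additional covariates into the models, including age, gender, baseline physical and mental health, BMI, expectancy", and exercise behaviour. The stated interest in age is whether it shrinks the random-effect variances: "We are particularly interested in examining age with a focus on assessing whether age substantially reduces the variability of the random effects", explained as "whether it explains a substantial proportion of between-person variability in baseline complexity and slope". For the secondary outcomes, "Analyses of secondary outcomes will follow the same general analytic approach".

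The sample size paragraph adds: "Our primary hypothesis, however, is an interaction effect". It does not name the factors of that interaction.

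Aim 3 is more explicit for the parallel hypothesis H.3.d. Its first model, on baseline data, has a group term, an age term and a group difference in the rate of change with age. A second, similar model uses 6-month data for the randomized participants and a three-level group variable.

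**The concern.** H.1.d is a statement about the difference between arms: it should be larger in older participants. How much between-person variance age explains is a different quantity, because it pools the arms. The background in B2 already expects complexity to fall with age, so a drop in random-intercept variance is likely whether or not H.1.d is true.

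As written, then, one of the four Aim 1 hypotheses has no analysis in the Aim 1 text that targets it. The one age result that is described could be taken as support for H.1.d, or as evidence against it, when it is neither. The primary treatment comparison is not affected.

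**Working it through.** **1. The plan's own figures.** No figure is given for the age analysis. The power figures do reproduce with alpha 0.05 two-sided (the level is assumed; two-sidedness is stated):
- Main effect, 30 per arm, SE = sqrt(2/30): 0.52 SD gives 50.8% and 0.74 SD gives 80.5%.
- Interaction, worst case, SE = sqrt(4/15): 1.03 SD gives 50.0%.
- Interaction, independent follow-ups, SE = sqrt(4/30): 0.72 SD gives 49.8% and 1.03 SD gives 79.9%.

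These do not say which interaction was meant.

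**2. What the variance criterion picks up.** Let age change a person's slope over time by b per year, and let the covariate model have one age x time term common to both arms.
- Same trend b in both arms (no modification): the fitted coefficient is b, and the slope variance removed is b² x var(age).
- Trend b in the Tai Chi arm only (modification b): the pooled coefficient is b/2, and the variance removed is b² x var(age)/4.
- Trends +b/2 and -b/2 (modification b again): the pooled coefficient is 0, and nothing is removed.

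So shrinkage is greatest here with no modification, and the same modification gives two different amounts of shrinkage.

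**3. Simulation with assumed values.** There were 2,000 runs of 60 people at 0, 3 and 6 months. Age was uniform, the random-intercept SD 1, the random-slope SD 0.6 and the residual SD 0.5. The direct test is treatment x age on person-level slopes.

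| Truth | Intercept variance cut | Slope variance cut | Direct test rejects |
|---|---|---|---|
| Age acts on baseline and equally on both slopes | 27% | 31% | 5.1% |
| Age acts on baseline only | 27% | about 0% | 4.8% |
| Modification, Tai Chi arm only | about 0% | 17% | 68% |
| Modification, opposite trends | about 0% | about 0% | 67% |

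The slope figures agree with step 2: 0.4²/(0.4² + 0.6²) = 0.31 for the common trend, and 0.3²/(0.6² + 0.6²/2) = 0.17 for the Tai Chi arm only. The first two rows have no modification and the last two have equal modification. Only the direct test separates the pairs.

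**4. What a direct term could detect.** With SD meaning the residual SD of person-level change, the SE of the modification per year of age is sqrt(1/30 + 1/30)/SD(age) = 0.258/SD(age). The multiplier for 80% power is about 2.85.
- Ages uniform over a 30-year span: SD = 30/sqrt(12) = 8.66. Then 0.258/8.66 = 0.0298, and x 2.85 = 0.085 per year, or 0.85 SD per decade.
- Ages uniform over 50 to 79: SD = 29/sqrt(12) = 8.37. Then 0.736/8.37 = 0.088 per year, or 0.88 SD per decade, which is 0.736 x 29/8.37 = 2.55 SD between ages 50 and 79.
- For 50% power, the second case gives 0.515/8.37 = 0.0615 per year, or 0.62 SD per decade.

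Both cases assume no dropout; the protocol gives no rate. If, for illustration, 20% were lost, the 80% figures would rise by 1/sqrt(0.8), to 0.95-0.98 SD per decade.

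**The case against.** The strongest reply is that a usable model already exists in Aim 3. The Study Design section describes novices as people after 6 months of training. At 6 months, the novice and naïve groups are then the two randomized arms. If the three-group model keeps the age terms of the first Aim 3 model, it yields a randomized difference in age slope. This stands, and it rules out saying that the trial cannot address H.1.d. But the model uses one time point and no baseline, is not tied to H.1.d, and has to be inferred: elsewhere the Aim 3 text calls all 60 randomized participants novices.

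Second, the protocol never claims that the variance comparison tests H.1.d. It is a sensitivity analysis and suits its own descriptive purpose. That is true. The gap is that the Aim 1 text describes one age analysis, and it answers a question other than the Aim 1 age hypothesis.

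Third, the model equations are not legible in the copy reviewed, and adding covariates does not exclude an interaction. So the claim can only be that no such term is stated. The prose makes treatment on slope the focal coefficient and introduces age only later.

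Two further inferences are tempting and should not be drawn. One is that variance shrinkage is identical with and without modification, or carries no information at all; step 2 shows that the amounts differ, and the fault is lack of specificity. The other is that the trial was sized for a treatment x age test. The 1.03 figure does match a 2x2 contrast with 15 people per cell, but the factors are not named.

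**Conclusion.** The point holds in a limited form. The age analysis described for Aim 1 cannot distinguish effect modification from a common age trend and can miss modification altogether, and no treatment x age x time term is stated there. The Aim 3 three-group model is a partial and unlabelled substitute.

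This is a modest defect in a pilot, concerning a hypothesis that is not the primary comparison. The conclusion about the criterion rests on the algebra; the percentages depend on the simulation values. A direct analysis would also have low power. The detectable 0.85-0.88 SD per decade rests on near-uniform ages, alpha 0.05, 30 analysed per arm and no dropout; dropout or a narrower age spread would raise it. The gain is therefore an interpretable estimate of the right quantity, and neither confirmation nor refutation of H.1.d should be expected.

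**What to change.** Add centred continuous age x treatment x time, with all lower-order terms, to the Aim 1 mixed model, for the primary complexity outcomes and for the secondary outcomes. State that this coefficient, per decade of age with its 95% confidence interval, is the analysis of H.1.d and is exploratory. Keep the random-effect variance comparison as a description of how age relates to baseline and slope, and say that it does not bear on H.1.d. In Aim 3, say whether the three-group model keeps its age terms and which participants form the naïve and novice groups.

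The cost is one extra low-powered exploratory model per outcome, with no adjustment for multiple testing planned. No new data are needed: age is already a stratification factor, and the model uses baseline and both follow-ups.
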